### Secondary objective/endpoints

Secondary end-points include; the individuals components of the primary composite end-point, incidence of metabolic syndrome as defined by the International Diabetes Federation (IDF) [11,12], incidence of pre-hypertension as defined by Joint National Committee on Prevention, Detection, Evaluation, and the Treatment of High Blood Pressure (JNC-7) [13], regression of IGT and IFG, [IGT and IFG will be defined as per World Health Organisation (WHO) and American Diabetes Association criteria [14,15]] and changes in: weight, BMI, waist circumference (WC), fasting triglycerides, fasting high density lipoprotein (HDL) and low density lipoprotein (LDL) cholesterol, serum creatinine and estimated glomerular filtration rate (GFR), physical activity as measured by the International physical activity questionnaire (IPAQ)[16], depression, as measured by PHQ-9 questionnaire, [17], and psychological stress, as measured by perceived stress scale [18]. Adherence to diet and physical activity will be self-reported based on weekly pattern and evaluated at study visits. The effects of baseline risk factors on the development of end-points will also be evaluated in analyses.

Quality of life measures will be evaluated using a validated short version of the multidimensional WHO Quality of Life questionnaire (WHOQOL-Bref) [19]. Health economic analyses by the Public Health Department University of Colombo with advice and guidance from Division of Social Care and Policy at King's College London is an area we plan to develop utilising models described in recent studies [20].

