## Methods/Design

### Study design

DIABRISK-SL is an open randomised controlled parallel group clinical trial evaluating the effect of intensive (3-monthly; study group) *vs*. less-intensive (12-monthly; control group) LSM advice on a primary composite cardio-metabolic end-point (new onset T2DM, IGT, hypertension, and albuminuria) in 'at-risk' young urban subjects aged between 5-40 years. The two arms of the study have 1:1 allocation ratio and follow up is over 5 years. Figure 1 details the trial flow chart.

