### Statistical methods and power calculation

Approximately 2300 subjects with ≥2 risk-factors are required in each group (4600 subjects in total) to detect a 25% relative risk reduction at 5 years on the primary composite cardio-metabolic end-point of new onset T2DM, IGT, IFG, hypertension, albuminuria, renal and CVD events with intensive LSM. The study is powered at the 90% level with a type-1 error of 0.05 (2 sided) assuming a 15% incidence of the primary end-point in the control group and including allowance for 25% drop-out of subjects. The proposed 25% relative risk reduction of the composite outcome is derived from the effects of intensive LSM programme reducing the relative risk of new onset T2DM in South Asian IGT patients [1,6].

There will be a pre-specified interim analysis of the composite primary and secondary endpoints at 2 years, as requested by one of the funding bodies (IDF BRIDGES). This analysis will be performed by an independent statistician and the trial investigators will remain blinded to the full data analyses and interim results. All data related to interim analysis will directly forwarded to funding body by the independent statistician and will be strictly confidential and not for public dissemination/publication.

Descriptive statistics will be used for the analysis of demographic and clinical features of the cohort. Two-sided t-tests and chi-square (χ^2^) tests will be used to analyze the comparison between the groups at baseline and during follow-up. Survival curves will be calculated to estimate the cumulative incidence of the composite primary end-point and secondary end-points. The difference between the groups in the primary end-point will be tested by means of the two-sided log-rank test. All analyses of end-points are based on the intention-to-treat principle. Analyses will be performed using STATA software version 10 (Stata Corp, College Station, TX, USA).

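### The primary log-rank test names no strata across ages 5-40; a few pre-specified baseline strata would gain roughly 0 to 5 points of power at almost no cost

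*Protocol article*

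**What the plan says.** All references are to the protocol article.

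- **Primary test** (Statistical methods and power calculation): "The difference between the groups in the primary end-point will be tested by means of the two-sided log-rank test". No strata or covariates are attached to it.
- **Design figures** (same section): "Approximately 2300 subjects with ≥2 risk-factors are required in each group (4600 subjects in total"), "to detect a 25% relative risk reduction at 5 years", "assuming a 15% incidence of the primary end-point in the control group" and "including allowance for 25% drop-out of subjects". On error rates: "The study is powered at the 90% level with a type-1 error of 0.05 (2 sided").
- **Design** (Study design): "The two arms of the study have 1:1 allocation ratio and follow up is over 5 years".
- **Randomisation**: a computer-generated sequence prepared by an independent party. No stratification factors are named.
- **Population** (Inclusion Criteria): ages 5-40 with at least two of four risk factors, namely family history, inactivity, raised BMI and raised waist circumference.
- **Data in hand before randomisation**: family history, activity and anthropometry from screening (Abstract; Study population and recruitment); anthropometry, blood pressure, glucose tolerance and other laboratory values at baseline (Procedures).
- **Stated use of the risk factors** (Secondary objective/endpoints): "The effects of baseline risk factors on the development of end-points will also be evaluated in analyses". This makes them predictors to be studied and does not bring them into the primary test.

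**The concern.** A single log-rank over all participants compares the arms without using anything known about baseline risk. If 5-year risk differs widely between, say, a young child with two risk factors and a 38-year-old with four, comparing like with like inside strata is more efficient. The article itself treats these factors as prognostic: the Background reports that inactivity, raised BMI and central obesity were strongly associated with dysglycaemia. The end-point definitions also change with age and sex (hypertension by percentile below 18 years, albuminuria with sex-specific cut-offs), so age and sex are natural strata.

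What is at stake is a modest amount of power in a design that, by its own accounting, sits almost exactly at its 90% target.

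**Working it through.** **1. Reproduce the plan's sample size.** Inputs: control risk 15%; intensive-arm risk 0.75 × 15% = 11.25%; two-sided alpha 0.05; power 90%; drop-out 25%.

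- Two proportions: n = [1.960·√(2 × 0.13125 × 0.86875) + 1.2816·√(0.15 × 0.85 + 0.1125 × 0.8875)]² / 0.0375² = 1,702 per arm, and 1,702/0.75 = 2,270. With continuity correction, 1,755/0.75 = 2,340.
- Equivalent hazard ratio: ln(0.8875)/ln(0.85) = 0.734.
- Schoenfeld: 4(1.960 + 1.2816)²/(ln 0.734)² = 441 events; 441/0.13125/2 = 1,680 per arm; 1,680/0.75 = 2,240.
- Freedman: 448 events, 2,276 per arm.

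All lie within 3% of the stated 2,300. With 0.75 × 2,300 = 1,725 evaluable per arm, power is 90.4% (two proportions) or 90.7% (Schoenfeld, 1,725 × (0.15 + 0.1125) = 453 events). The 90% claim holds without stratification.

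**2. Approximate gain from stratifying.** Let R² be the share of outcome variance explained by the strata: R² = Σ pₛ(riskₛ − 0.15)²/(0.15 × 0.85). The effective size is then about 1,725/(1 − R²) per arm. The article gives no incidence by age, sex or risk-factor count and no age mix of those randomised, so R² is an assumption.

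| R² assumed | Power | Gain over 90.38% (points) |
|---|---|---|
| 0.02 | 90.93% | 0.55 |
| 0.05 | 91.75% | 1.37 |
| 0.10 | 93.06% | 2.68 |
| 0.15 | 94.30% | 3.91 |
| 0.20 | 95.44% | 5.06 |

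A case that can be checked by hand, on assumed values: four equal age bands with control risks of 3%, 7%, 17% and 33% average 15%. Their variance is (144 + 64 + 4 + 324)/4 = 134 in squared percentage points, or 0.0134, so R² = 0.0134/0.1275 = 0.105.

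**3. Simulation of the stratified log-rank.** Settings: 1,725 per arm, 5 years, annual detection, overall risks held at 15% and 11.25%, 4,000 runs per row. There were 12 strata: three age bands (40/30/30%), sex (50/50) and risk-factor count (60/40). The mix and the hazard ratios are assumptions.

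| Hazard ratios: oldest vs youngest age band, sex, count | R² | Lowest to highest stratum risk, control | Gain, constant hazard ratio | Gain, constant relative risk |
|---|---|---|---|---|
| 2, 1.1, 1.3 | 0.016 | 9.3-24.4% | 0.15 | 0.55 |
| 3, 1.2, 1.5 | 0.039 | 6.7-31.2% | 0.90 | 0.93 |
| 4, 1.3, 1.5 | 0.058 | 5.4-35.1% | 1.45 | 1.65 |
| 6, 1.3, 1.8 | 0.095 | 3.8-41.8% | 2.23 | 2.30 |
| 10, 1.5, 2 | 0.146 | 2.3-50.4% | 3.70 | 3.52 |
| 15, 1.5, 2.5 | 0.196 | 1.5-57.5% | 4.45 | 4.70 |

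**4. Strata that capture only part of the risk.** Age, sex and a count are proxies for true risk. In simulations with a normally distributed log-hazard (1,500 runs, Monte Carlo error about 0.7 points on each power), the gains were:

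- strata capturing 50% of the log-hazard variance: +0.5, +1.3 and +2.1 points at SD 0.5, 1.0 and 1.5;
- strata capturing 25%: +0.1, +0.5 and +0.7 points.

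Capturing all of an SD of 1.0 to 1.5 gave about +2 to +5.

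**5. Downside.** With no treatment effect, 12 strata and R² 0.095, type I error was 5.1% stratified and 4.8% unstratified (6,000 runs; standard error √(0.05 × 0.95/6,000) = 0.3 points). With eight strata that predict nothing, power fell by 0.07 points.

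**6. Drop-outs who contribute person-time.** With 2,300 per arm, gradual drop-out reaching 25% at 5 years, and eight strata with control risks of 2.5% to 41.8%, power went from 93.8% to 95.5%: +1.7 points, against +2.9 in the same scenario with 1,725 completers per arm.

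**The case against.** The strongest reply is that nothing here is wrong. The log-rank test is valid, the analysis is by intention to treat, and the promised power is delivered. All of that stands, and it limits the point to efficiency.

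A second reply is that a condensed article leaves strata to a full protocol or analysis plan. The article never calls the test unstratified, and a document not shown may add strata. That is a fair caution. But the article does name the primary test, and as written it is a plain log-rank; a better choice for a test that is stated is not a complaint about missing detail.

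A third reply is that the spread in risk may be modest. Paediatric hypertension, BMI and waist criteria are percentile-based, and people with diagnosed end-points are excluded, both of which may flatten the age gradient. This stands, and it is why the low end of the range must be shown.

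Several stronger readings are tempting but unsupported:

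- **Bias from chance imbalance.** A reader might infer that an unstratified test after unstratified randomisation leaves a biased result. Chance imbalance is already covered by the type I error and should be small at about 2,300 per arm.
- **An attenuated effect.** The unstratified hazard ratio is a marginal quantity and the stratified one is conditional. In the eight-stratum scenario with risks of 2.5% to 41.8%, a within-stratum ratio of 0.721 corresponds to the same 15% vs 11.25% that gives 0.734 without strata. That is a difference of estimand and not a bias.
- **A fixed gain of 3-4 points, or the equivalent of 14-20% more participants.** By 1/(1 − R²), 14-20% needs R² of 0.12 to 0.17 (1 − 1/1.14; 1 − 1/1.20). Nothing in the article establishes such values.
- **An offset for participants who already meet an end-point at baseline.** That is a separate matter, and nothing here measures it.

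**Conclusion.** The point holds as a nearly free improvement. The primary test as stated is valid and meets its 90% power, but it makes no use of prognostic factors recorded before randomisation in a population spanning 35 years of age.

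Stratifying gains about 0 to 2 points of power if the strata capture part of a modest to large spread in risk, and up to about 5 points if they capture most of a large one. Expressed through R², 0.02 to 0.20 corresponds to roughly +0.5 to +5 points. The gain shrinks if drop-outs contribute follow-up before leaving.

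These figures rest on the plan's 15% vs 11.25%, on 1,725 evaluable per arm, and on assumed prognostic strengths that the article does not supply. The direction is more secure than the size: power rose in every simulated scenario with prognostic strata, and the cost when strata were uninformative was negligible.

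**What to change.** State that the primary test is a two-sided log-rank stratified by a few baseline factors, for example age band (three or four bands, with a break at 18 years where the end-point definitions change), sex, and number of risk factors (2 vs 3-4). Report the hazard ratio and 95% CI from a Cox model stratified in the same way. Keep the unstratified log-rank as a sensitivity analysis.

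Fix the strata and cut-points before anyone choosing them has seen outcomes by arm, including the 2-year interim results. Keep the strata few: 453 expected events over 12 strata is about 38 per stratum on average, and fewer in the low-risk ones.

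The cost is a sentence or two of wording. No participants, visits or measurements are added; risk-factor count and age should be known for everyone because eligibility depends on them. The one consequence to state in the report is that the hazard ratio is conditional on the strata, so the 5-year cumulative incidence by arm should be shown beside it.

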### Definition of primary cardio-metabolic end-points

▪ **New onset T2DM **as indicated by either a fasting plasma glucose of ≥7.0 mmol/l and/or a 2-hr plasma glucose concentration of ≥11.1 mmol/l during an annual follow-up confirmed by repeat 75 g OGTT as per World Health Organization (WHO) criteria [14] or initiation anti-diabetic treatment by the subject's family physician following confirmatory tests.

▪ **New onset IGT **is defined as a plasma fasting glucose <7.0 mmol/l and 2-h glucose 7.8-11.0 mmol/l and IFG as fasting plasma glucose between 6.1 to.9 mmol/l or 5.6 to 6.9 mmol/l [14,15].

▪ **New onset hypertension **is defined as mean brachial blood pressure from 2 readings taken following 5 minutes rest ≥140/90 mmHg or initiation of anti-hypertensive treatment commenced by the subject's family physician as per JNC-7 criteria [13]. In those below 18 years hypertension is defined as blood pressure that is, on repeated measurement, at the 95^th ^percentile or greater adjusted for age, height, and sex [13].

▪ **New onset albuminuria is defined as **urine albumin/creatinine ratio ≥2.5 mg/mmol in males and ≥3.5 mg/mmol in females from early morning sample confirmed on one repeat test.

▪ **New onset renal impairment is **defined as estimated GFR <60 ml/min or doubling of serum creatinine from baseline.

▪ **CVD events **are defined as fatal and not fatal events of Myocardial infarction (MI): Congestive heart failure (CHF): death due to clinical, radiological or post-mortem evidence of CHF, Stroke, vascular revascularisitation and admission for unstable angina.

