#### During the primary prevention intervention trial

• Subjects who reach one or more of the following cardio-metabolic end-points; T2DM, CVD, hypertension, and albuminuria.

• Subjects initiated on any form of medication used for the treatment of diabetes, hypertension, renal disease or dyslipidaemia by their family physician or other medical physician.

• Pregnancy at any stage of the study

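### A drug start counts as a T2DM or hypertension event only if the family physician made it, yet the in-trial exclusion removes participants treated by any physician, so true events can be lost

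*Protocol article*

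**What the plan says.** Under Definition of primary cardio-metabolic end-points, T2DM and hypertension each have two routes to an event. One is a measured value: fasting or 2-hour glucose at an annual follow-up, confirmed by a repeat OGTT, or a mean resting blood pressure at or above 140/90 mmHg. The other is a treatment start. For T2DM that is "initiation anti-diabetic treatment by the subject's family physician following confirmatory tests"; for hypertension it is "initiation of anti-hypertensive treatment commenced by the subject's family physician as per JNC-7 criteria". No other prescriber is named in either clause. For participants below 18 years, hypertension is defined by a blood pressure percentile on repeated measurement, and that sentence does not mention treatment.

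Under Exclusion Criteria, the list for the intervention trial itself covers participants who reach an end-point and, separately, those started on medication "for the treatment of diabetes, hypertension, renal disease or dyslipidaemia by their family physician or other medical physician".

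Under Statistical methods and power calculation, the primary end-point is compared by a two-sided log-rank test, and all end-point analyses follow intention to treat. That section does not say how a participant removed after a drug start enters the analysis.

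**The concern.** The protocol itself expects doctors other than the family physician to start these drugs, because its exclusion rule names them. It removes such participants but does not count the start as an event. Whether a true case of diabetes or hypertension enters the primary end-point can thus depend on who wrote the prescription.

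The measured route is not a reliable backstop. For T2DM it operates at annual follow-up. A participant treated by a hospital or specialist doctor between visits may leave before the next test, or be tested while on treatment. In the first case the reason for censoring is the very disease being counted, which breaks the independent-censoring assumption of the log-rank test. In the second the drug may hide the event. Removing the exclusion rule would cure the first path but not the second, so the end-point wording needs attention in its own right. No stated review step would recover these cases: the independent board adjudicates CVD events only.

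**Working it through.** **1. The two rules side by side**

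| Who starts the drug | Counts as T2DM or hypertension event? | Falls under the in-trial exclusion? |
|---|---|---|
| Family physician (after confirmatory tests, or per JNC-7) | Yes | Yes, but the event is already counted |
| Another physician, same diagnostic basis | Not by the treatment clause | Yes |

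The second row is the gap. Such a participant becomes an event only through a study measurement or another component of the composite.

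**2. Design inputs** (Statistical methods and power calculation): "The study is powered at the 90% level"; "assuming a 15% incidence of the primary end-point in the control group"; "detect a 25% relative risk reduction at 5 years"; "including allowance for 25% drop-out of subjects"; two-sided 5% error; about 2300 per arm.

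The intensive-arm risk is 0.15 × 0.75 = 0.1125.

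**3. Reproducing the stated sample size** (two proportions, normal approximation)

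n = (1.960 + 1.2816)² × (0.15 × 0.85 + 0.1125 × 0.8875) / 0.0375² = 1699 per arm.

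1699 / 0.75 = 2266 per arm, against a stated 2300. A log-rank calculation with the implied hazard ratio ln(0.8875)/ln(0.85) = 0.734 gives 2240 (Schoenfeld) or 2276 (Freedman) per arm. The stated figure reproduces.

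**4. Base power**

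Evaluable per arm: 2300 × 0.75 = 1725.

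Power = Φ(0.0375 / √[(0.1275 + 0.0998)/1725] − 1.960) = Φ(3.267 − 1.960) = 90.4%.

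Expected events: 1725 × 0.15 + 1725 × 0.1125 = 259 + 194 = 453.

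**5. Sensitivity to lost events**

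The document gives no share of first prescriptions by other doctors, so the shares below are assumptions. Let s_C and s_I be the fractions of composite events lost in the control and intensive arms. Then p_C = 0.15(1 − s_C), p_I = 0.1125(1 − s_I), and the apparent relative risk reduction (RRR) is 1 − p_I/p_C.

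| Lost, control | Lost, intensive | Apparent RRR | Power |
|---|---|---|---|
| 0% | 0% | 25.0% | 90.4% |
| 1% | 1% | 25.0% | 90.1% |
| 3% | 3% | 25.0% | 89.4% |
| 5% | 5% | 25.0% | 88.7% |
| 10% | 10% | 25.0% | 86.8% |
| 5% | 2.5% | 23.0% | 82.8% |
| 2.5% | 5% | 26.9% | 93.6% |
| 10% | 5% | 20.8% | 71.8% |
| 5% | 10% | 28.9% | 96.0% |

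An equal 5% loss is about 0.05 × 453 = 23 events. In the unequal rows, power means the chance of a significant result on the distorted contrast. A higher figure there reflects bias, not a better trial.

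The shares are fractions of the whole composite, although only T2DM and hypertension have a treatment route. A given share among T2DM and hypertension events is a smaller share of all primary events, so the larger rows are outer illustrations.

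**The case against.** Several points on the other side are sound.

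- **Scored event-free.** A reader might infer that participants treated by another doctor are recorded as event-free. Nothing in the protocol says so. Under the exclusion rule they would most likely be censored at drug start; if they stay in follow-up, the measured criteria still apply.
- **Recovery through the composite.** A treated diabetic whose fasting glucose stays in the IFG band, or whose 2-hour value stays at 7.8–11.0 mmol/l, is still a primary event under the stated objective. Many T2DM cases could also have counted earlier as IGT or IFG. Masking is therefore mainly a hypertension question, and possible rather than certain.
- **Direction.** It is tempting to argue that control participants, with one contact a year against four, are more often picked up first by outside doctors, so that the trial is biased towards no effect. The document does not support that. The intensive contacts are described as advice and progress review, and no blood pressure or glucose test is stated for them. More contact could equally send intensive participants to a doctor. The sensitivity table runs both ways, and its 72% row is only one corner of an assumed grid.
- **Source of the censoring.** That path comes partly from the exclusion rule, which is a wider issue than the prescriber wording.
- **Below 18 years.** The percentile sentence may replace only the adult threshold and leave the treatment clause in force. The text is unclear rather than a definite omission.
- **Loose wording.** Family physician may be meant as shorthand for any doctor outside the trial, and a fuller protocol may say so.

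These points reduce the likely size. They do not remove the mismatch: the same article uses the wider wording in one section and the narrower in another, and the narrower one defines the primary event.

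**Conclusion.** The concern holds in a limited form. As written, the treatment clauses for T2DM and hypertension are narrower than the protocol's own in-trial exclusion, so a true event first treated by another doctor can be censored informatively, contrary to the stated intention-to-treat principle, or possibly missed on treatment.

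Neither the amount nor the direction of bias can be determined from the document. If the loss is small and equal between arms, the cost is slight: up to 5% of composite events takes power from 90.4% to no lower than 88.7%. If the loss is unequal, the apparent relative risk reduction moves away from 25% in whichever direction the imbalance runs. Both statements rest on the protocol's 15% control risk, 25% reduction and 25% drop-out, on assumed loss shares, and on a two-proportion approximation to the log-rank test. The sample size needs no change.

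**What to change.** In both treatment clauses under Definition of primary cardio-metabolic end-points, make the prescriber wording match the in-trial exclusion, so that treatment started by any physician counts. Keep the existing conditions: confirmatory tests for T2DM and JNC-7 criteria for hypertension. Date the event at treatment start. State that these participants count as events in the primary analysis, whatever happens to their later participation. State whether the hypertension treatment clause also applies below 18 years.

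This concerns event definition and analysis only and changes nothing in how participants are managed. It costs a wording change in two definitions, one clarifying sentence for those below 18, and an occasional request for outside medical records. No extra participants, visits or tests are needed.

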### Inclusion Criteria for primary prevention intervention trial

Subjects aged 5-40 years with two or more risk factors for cardio-metabolic disease. The risk factors for selection included two or more of the following;

• ***First degree FH of T2DM***

• ***Physical inactivity***

• ***Raised BMI***

• ***Raised WC***

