#### Procedures

The following procedures and measurements will be performed at baseline prior to randomisation to one of the two groups.

Height is measured using a portable stadiometer (Seca France) and taken to the closest 0.1 cm, and weight is measured without footwear in light clothing to the nearest 100 g with an electronic weighing scale (Seca France). Both instruments are calibrated weekly. BMI is calculated as weight in kilograms divided by height squared in meters. WC is measured using a graduated measuring tape (Seca France), calibrated weekly, with a locking device to the nearest 0.1 cm. WC is taken at the mid-point between the iliac crest and the last rib in expiration. Blood pressure is measured by automatic oscillometry from the non-dominant arm after 5 minutes rest with the mean of two measurements recorded (Riester Ri-Champion Riester, Jungingen, Germany). WHO approved growth charts for male and female children will be used [24].

Fasting plasma glucose and a standard 2-hour 75 g oral glucose tolerance test (OGTT) is performed in adults and glucose solution 1.75 g/kg body weight, to a maximal dose of 75 g is given to those below 16 years following a 12-hour fast as per WHO guidelines [14]. Plasma Glucose, total cholesterol, high density density lipoprotein (HDL), low density lipoprotein (LDL), triglycerides and serum creatinine will be measured by enzymatic colorimetry (Vitros MS 250, Ortho Clinical Diagnostics, Johnson and Johnson, Co, Rochester USA). Fasting plasma insulin will be measured using radioimmunoassay (Immulite, Siemens, Surrey, UK), which has a sensitivity of 4 μU/ml (<24 pmol/l) and intra and interassay coefficients of variation <8%. Insulin resistance will be calculated using the homeostasis model assessment of insulin resistance (HOMA-IR) [25]. Urine albumin to creatinine ratio will be measured by immunoturbidemtry (Vitros 5,1 FS Chemistry System, Ortho-Clinical Diagnostics, Johnson and Johnson Company, Hampshire, United Kingdom) from an early morning urine sample. In subjects below 18 years the Schwartz equation will be used to estimate glomerular filtration rate (GFR) from serum creatinine values [26] and in subjects above 18 years the Modification of Diet in Renal Disease (MDRD) Study equation will be used to estimate GFR [27].

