#### Independent advisory and data monitoring group

An independent external expert advisory and monitoring board has been formulated which includes two experts from the MV-Diabetes Research Centre and Hospital in Chennai India (IDPP trial site) and one Sri Lankan expert from the Department of Community medicine, University of Colombo. This board will regularly review the progress of the DIABRISK-SL study and will also independently adjudicate on CVD events.

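### The renal end-point counts a doubling of raw serum creatinine at every age from 5 without allowing for growth, so some healthy adolescents can be scored as renal impairment; the effect on the composite is small.

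*Protocol article*

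**What the plan says.** The section Definition of primary cardio-metabolic end-points lists new onset renal impairment, "defined as estimated GFR <60 ml/min or doubling of serum creatinine from baseline". The two limbs are joined by an or, so a creatinine doubling counts whatever the eGFR. No age limit, growth adjustment or repeat test is attached.

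The trial enrols "Subjects aged 5-40 years with two or more risk factors for cardio-metabolic disease", and "The two arms of the study have 1:1 allocation ratio and follow up is over 5 years".

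Other measures are adapted to children or confirmed:
- Procedures: "In subjects below 18 years the Schwartz equation will be used to estimate glomerular filtration rate (GFR) from serum creatinine values"; above 18 the MDRD equation is used.
- Hypertension, in the same list of definitions: "In those below 18 years hypertension is defined as blood pressure that is, on repeated measurement", with percentiles adjusted for age, height and sex.
- Albuminuria, in the same list: "from early morning sample confirmed on one repeat test".
- The advisory and monitoring board "will also independently adjudicate on CVD events"; adjudication of renal events is not mentioned.

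The article is inconsistent on whether renal impairment is a primary event. Statistical methods and power calculation sizes the trial on "new onset T2DM, IGT, IFG, hypertension, albuminuria, renal and CVD events with intensive LSM", and the definitions section lists renal impairment under its primary heading. The Abstract, Primary objective/end-point and Study design sections name the composite without renal events.

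**The concern.** Schwartz-type equations estimate GFR as a constant times height divided by serum creatinine. If true GFR stays the same while a child grows, creatinine must rise with height. It must rise further in adolescent boys if the version used has a larger constant for them. A fixed ratio to a childhood baseline therefore partly measures growth.

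The two limbs of the definition can then disagree. Suppose a boy has a baseline eGFR of 120 and a growth-expected creatinine ratio of 1.56 (both assumed). If his observed creatinine doubles, his Schwartz eGFR is 120 x 1.56 / 2 = about 94. The eGFR limb places him far above 60, yet the creatinine limb scores renal impairment.

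At stake are the meaning of the renal component in adolescents and, if renal events are primary, some dilution of the treatment effect.

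**Working it through.** **1. The plan's own figure.** Inputs from the power section: control incidence 15%, 25% relative reduction (so 11.25%), two-sided alpha 0.05, power 90%, 25% drop-out.

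n per arm = [1.960 x sqrt(2 x 0.13125 x 0.86875) + 1.282 x sqrt(0.15 x 0.85 + 0.1125 x 0.8875)]² / 0.0375² = 1702. Dividing by 0.75 gives 2270, or 2340 with a continuity correction (1755 / 0.75). The stated figure of about 2300 is reproduced. With 2300 x 0.75 = 1725 completers per arm, power is 90.4%. Planned events before drop-out are 2300 x 0.15 + 2300 x 0.1125 = 345 + 259 = 604.

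**2. Expected creatinine ratio from growth.** The article names the Schwartz equation but does not print it and gives no heights, so these inputs are assumptions: form k x height / creatinine, median heights, k = 0.55 rising to 0.70 in boys from about 13, unchanged GFR.

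Ratio = (height ratio) x (k ratio). The step in k contributes 0.70 / 0.55 = 1.27.

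| Age at entry to year 5 | Expected ratio |
|---|---|
| Girl 8 to 13 | 1.23 |
| Boy 5 to 10 | 1.25 |
| Boy 8 to 13, or 10 to 15 | 1.56 |
| Boy 12 to 17 | 1.49 |

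All are below 2.

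**3. Chance of an observed doubling at one year-5 reading.** P = 1 - Phi[ ln(2 / ratio) / (sqrt(2) x CV) ], where CV is the total variation per reading (assumed). For ratio 1.56, ln(2 / 1.56) = 0.248.

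| Ratio | CV 5% | CV 10% | CV 15% |
|---|---|---|---|
| 1.56 | 0.02% | 3.9% | 12.1% |
| 1.49 | about 0% | 1.9% | 8.3% |
| 1.25 | about 0% | 0.04% | 1.3% |
| 1.23 | about 0% | 0.03% | 1.1% |

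**4. Number of false events.** The article gives no age breakdown of randomised subjects. Assume that boys aged 8 to 12 at entry are 5% to 10% of 4600, that is 230 to 460, and give all of them ratio 1.56.
- CV 5%: 460 x 0.0002 = about 0.1 at most.
- CV 10%: 230 x 0.039 = 9 to 460 x 0.039 = 18.
- CV 15%: 230 x 0.12 = 28 to 460 x 0.12 = 55.

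**5. Effect on the composite, if renal events are in it.** Let f be the share of otherwise event-free subjects falsely scored, equal in both arms. The control rate becomes 0.15 + 0.85f and the intensive rate 0.1125 + 0.8875f.

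| False events of 4600 | f | Rates | Relative reduction | Power at 1725 per arm |
|---|---|---|---|---|
| 0 | 0 | 15.0% v 11.25% | 25.0% | 90.4% |
| 18 | 0.39% | 15.3% v 11.6% | 24.4% | 89.5% |
| 55 | 1.20% | 16.0% v 12.3% | 23.1% | 87.7% |

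**The case against.** Much of the opposing case stands.

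- **Primary status is unsettled.** Three sections leave renal events out of the composite. If they govern, no primary event arises from creatinine and step 5 falls away. A reader might infer that healthy children will be scored as primary events; the article does not settle that.
- **Growth alone does not double creatinine.** At a CV of 5% the problem nearly vanishes, so the range of false events starts near zero. The figure of 55 needs the highest CV, the highest ratio and the largest share of boys together.
- **The size rests on outside inputs.** The step in the Schwartz constant does most of the work: without it, at ratio 1.25 and CV 10%, the chance is 0.04%.
- **No arm is favoured.** Randomisation makes such events largely non-differential, so a reading of bias towards one group is not supported.
- **The renal component is not worthless in children.** Its eGFR limb already uses a child-specific equation, and change in eGFR is a separate secondary end-point.
- **The missing repeat test is a weak contrast.** IGT and IFG have none either.

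It can also be said that a journal article leaves child-specific rules to the full protocol. That does not dispose of the point. The article prints a complete rule for everyone from age 5, and the rule as printed can contradict the article's own child eGFR.

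**Conclusion.** The definition is unsound for growing participants, but the consequence is modest. Under the assumptions above, about 0 to 55 false renal events could occur among 4600, mainly in boys crossing puberty; in girls and younger boys the chance is about 1% or less. If renal events are primary, the relative risk reduction stays at about 23% or above and power at about 87.7% or above. These limits belong to the assumed heights, constants, CV and share of boys, and to a single comparison at year 5. A reader might multiply the risk by assuming yearly creatinine readings; the article does not say how often creatinine is measured during follow-up, so that is not counted here.

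The main harm is to the renal component in adolescents, where growth plus measurement variation could supply part of what is counted. Separately, the sections that include renal events in the composite and those that omit them must be reconciled.

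**What to change.** In Definition of primary cardio-metabolic end-points, for participants under 18 at baseline, replace the creatinine-doubling limb with a halving of height-based (Schwartz) eGFR from baseline. At fixed height and constant this is the same change as a doubling of creatinine. Keep creatinine doubling for adults.

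Name the version of the equation and its constants in advance, and use that equation at baseline and at follow-up even after the participant passes 18. Without this, someone aged 14 to 17 at entry, who is 19 to 22 at year 5, would have a Schwartz baseline compared with an MDRD follow-up, which would create a new artefact.

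State in every section whether renal impairment belongs to the primary composite.

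The cost is small. Creatinine is already measured, and children's height is recorded at each visit. Those who pass 18 need one extra eGFR calculation, with height available at that time. Slightly fewer renal events will be counted. A confirmatory repeat sample is optional and not needed for this fix.
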